## Abstract

**Background:**

A large proportion of patients with spinal cord injury (SCI) regain ambulatory function. However, during the first 3 months most of the patients are not able to walk unsupported. To enable ambulatory training at such an early stage the body weight is partially relieved and the leg movements are assisted by two therapists. A more recent approach is the application of robotic based assistance which allows for longer training duration. From motor learning science and studies including patients with stroke, it is known that training effects depend on the duration of the training. Longer trainings result in a better walking function. The aim of the present study is to evaluate if prolonged robot assisted walking training leads to a better walking outcome in patients with incomplete SCI and whether such training is feasible or has undesirable effects.

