**Methods/Design:**

Patients from multiple sites with a subacute incomplete SCI and who are not able to walk independently will be randomized to either standard training (3-5 sessions per week, session duration maximum 25 minutes) or an intensive training (3-5 sessions per week, session duration minimum 50 minutes). After 8 weeks of training and 4 months later the walking ability, the occurrence of adverse events and the perceived rate of exertion as well as the patients' impression of change will be compared between groups.

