**Figure 1 F1:**
[figure not shown]
**The Lokomat is an actuated robotic exoskeleton for the training of ambulatory function on a moving treadmill**. The patient is secured by an overhead suspension system which partially reliefs the body weight. Position sensors and force transducers are used to monitor the efforts of the patient (Picture by courtesy of Hocoma AG).

Patients with mild para- or tetraparesis become ambulatory within days or weeks without being trained using special forms of therapy e.g. BWSTT or Lokomat. In contrast, SCI subjects presenting with an incomplete but severe spinal paresis (i.e. ASIA B and C) are referred to an intensive and specific locomotor training by the Lokomat. So far this algorithm is based on expert consensus [9].

The strategy of rehabilitation after SCI or stroke is based on the principles of motor learning. Important characteristics of exercises have been identified. Beside task-specificity, task-variability, feedback or contextual interference the amount of exercise seems to be a key element [10,11]. The improvement of motor performance within rehabilitation may be due to true recovery or compensation [12]. Nevertheless, the above mentioned principles are valid regardless the underlying mechanism [11].

A meta analysis including studies of patients with stroke showed that augmented exercise therapy had a favorable effect on activities of daily living [13] and longer training duration was correlated with improved walking performance (positive dose-response relationship) [14]. One of the advantages of robotic devices like the Lokomat is the ability to prolong time for locomotor training compared to manually assisted training [15]. Yet it is not clear whether longer training duration results in an improved outcome or if certain endpoints in terms of walking capacity can be achieved within a shorter period of time.

The aim of the present study is therefore to evaluate whether SCI patients with severe sensory-motor deficit after acute traumatic SCI (ASIA B and C) profit from prolonged Lokomat training compared to patients who undergo the usual training paradigm. The hypothesis is that patients with a severe but incomplete SCI who undergo a prolonged Lokomat training achieve higher grades of walking ability compared to their counterparts who complete the training as suggested by experts.

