### Subjects

Patients with a subacute traumatic SCI initially categorized as ASIA B or C with a motor level between C4 and T12 and who are only partially able to walk (Walking Index for Spinal Cord Injury-WISCI ≤5 [17]) will be eligible. Subjects should be able to start the training within 60 days after trauma. Patients who do not comply to the requirements of the Lokomat training device (i.e. bodyweight >130 kg, body height >200 cm, leg length diff >2 cm, osteoporosis, instable fracture of lower extremity, restricted range of motion, decubitus ulcer of lower extremity) or with concomitant injury limiting walking ability (e.g. lower extremity fractures, instable spine fractures, Joint instability preventing weight-bearing, severe soft tissue lesion, traumatic brain injury) or with pre-existing medical conditions interfering with unrestricted walking (e.g. total joint replacement, chronic pain, osteoarthritis, polyneuropathy, cardiopulmonary disease) or who are older than 60 years or younger than 18 years will be excluded from participation. Patients who already participate in other rehabilitation or pharmacological study will also not be considered for participation.

In previous studies with stroke subjects [18-23] the mean difference in walking speed amounted to 0.0418 m/s. This value was used to calculate the sample size further assuming a standard deviation of 0.05 m/s, a statistical power of 0.8 and a significance level of 0.05. The calculation resulted in the requirement of 23 subjects in each group to be able to reject the null hypothesis.

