### Outcome

Outcome data will be assessed in the respective centers by therapists and medical doctors. Hereafter the data will be sent anonymously to the PI for analyses. Due to the characteristic of this study neither the therapists nor the assessors nor the patients can reliably be blinded regarding the group allocation. The principal investigator (PI) who is the first author of this report (MW) and will be involved in the analyses will not be aware of the respective intervention.

In order to describe the characteristics of the included subjects, demographic and clinical data will be assessed. The primary outcome is the self selected walking speed using the Ten Meter Walking Test (TMWT) [24]. It will be assessed at baseline, bi-weekly during training, and at the six months follow-up. In addition the following items will be assessed at baseline, bi-weekly during training, and after six months: the Walking index for spinal cord injury -WISCI [17] (an ordinal scaled index for the assessment of walking capabilities with 21 categories. Zero represents that the patient is not able to stand or walk, the maximum of 20 means that the patient can walk without bracing, walking aids or personal assistance), the maximum walking speed, the ASIA classification [1], the detailed Spinal Cord Independence Measure-SCIM [25], the modified Ashworth scale-MAS [26] of hip and knee joints, and the Penn spasm frequency scale [27]. During the training period the mechanical stiffness and the maximum voluntary torque of the legs as well as the cooperation of the patient during the training will be assessed bi-weekly using the force transducers of the robotic training device. For every training the distance walked, walking speed, walking time and body weight unloading, the rate of perceived exertion as well as the occurrence of any events (e.g. skin breakdown or joint stress or scheduling problems) will be assessed. At the end of the training period, i.e. after 8 weeks the patients subjective impression about the success of the training will be assessed using the Patients' Global Impression of Change Scale-PGIC [28].

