### Analyses

All analyses will be performed in the leading center by the PI. He receives the data in form of an electronically completed case record form after completion of the training. For the analyses, the data will then be incorporated into the statistical software (PASW statistics 17.0, IBM-SPSS Inc. Chicago/IL).

In order to describe the characteristics of the sample, descriptive statistics will be applied. For the analysis of training induced differences between intervention and control group, T-Test for independent groups or the non-parametric correspondent depending on the outcome variable will be applied. In addition, multilevel models will be used to evaluate potential confounding factors (e.g. center effects, age differences, neurological level of lesion or ASIA) as required.

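### Ten-metre walking speed, the primary outcome, has no stated value for patients who cannot walk 10 m, and the analysis or the sample size fails whichever way they are handled

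*Protocol article*

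**What the plan says.** All references are to the protocol article.

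- **Outcome** names the variable: "The primary outcome is the self selected walking speed using the Ten Meter Walking Test (TMWT"). On timing it adds: "It will be assessed at baseline, bi-weekly during training, and at the six months follow-up".
- **Subjects** sets the walking criterion as patients "who are only partially able to walk (Walking Index for Spinal Cord Injury-WISCI ≤5 [17]) will be eligible". There is no lower limit. Outcome explains the bottom of that scale: "Zero represents that the patient is not able to stand or walk".
- **Abstract** describes patients "who are not able to walk independently will be randomized" and says that "during the first 3 months most of the patients are not able to walk unsupported".
- **Background** gives ASIA B patients a 50% chance of becoming ambulatory, with no time point. Its hypothesis is that patients with prolonged training "achieve higher grades of walking ability compared to their counterparts who complete the training as suggested by experts".
- **Analyses** gives the between-group method: "T-Test for independent groups or the non-parametric correspondent depending on the outcome variable will be applied".
- **Subjects** also sizes the trial: difference 0.0418 m/s, SD 0.05 m/s, power 0.8, significance level 0.05, 23 per group.

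No section gives a value, a rank or an exclusion rule for a patient who cannot complete the ten-metre test.

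**The concern.** The primary variable is undefined for part of the population that the article admits. This can matter after baseline too. Training starts at about day 30, and by day 60 at the latest, and lasts 56 days, so it ends at about day 86 to 116 after injury. Some patients may still be unable to walk 10 m then.

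Two treatments of these patients are open, and each causes a different problem.

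- **Compare recorded speeds only.** Membership of the compared set then depends on walking, which is observed after randomisation and which the training is meant to change. If longer training turns non-walkers into slow walkers, they pull down the intervention mean, and the comparison penalises the success that the hypothesis describes.
- **Score non-walkers as 0 m/s.** The randomised comparison is kept, but the outcome becomes a cluster of zeros plus a spread of speeds. An SD of 0.05 m/s does not describe that distribution.

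If the choice is made after the data are seen, it can decide the sign of the primary result.

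**Working it through.** **1. The article's own sample size.** Inputs from Subjects: d = 0.0418, SD = 0.05, power 0.8, level 0.05 (taken as two-sided).

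n = 2 × [SD × (1.960 + 0.842) / d]² = 22.46, rounded up to 23 per group. The stated figure reproduces. Power at 23 is 0.81 by the normal formula and 0.79 by the t distribution. The calculation counts every patient as having a speed.

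**2. Recorded speeds only: direction.** Assumptions: 50% of controls walk, at a mean of 0.40 m/s. The intervention leaves these patients unchanged and adds 20% of patients who walk at 0.10 m/s.

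| Comparison | Control | Intervention | Difference |
|---|---|---|---|
| Walkers only | 0.400 | (0.5 × 0.40 + 0.2 × 0.10) / 0.7 = 0.314 | −0.086 |
| All randomised, non-walkers 0 | 0.5 × 0.40 = 0.20 | 0.5 × 0.40 + 0.2 × 0.10 = 0.22 | +0.02 |

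The walkers-only difference is about twice the planned effect (0.086 / 0.0418 = 2.1), with the wrong sign.

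In simulated trials of this scenario with 23 per arm, the walkers-only t-test was significant in about 39% with an established-walker SD of 0.05, 22 to 23% at 0.15, and 16 to 18% at 0.20. Nearly all of these rejections pointed to harm.

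**3. When the sign reverses.** Let 50% of controls walk at mean m, let established walkers gain g, and let an extra share e newly walk at mean v. The walkers-only difference is negative when e × (m − v) > 0.5 × g.

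- With g = 0.0418, the new walkers must be slower than control walkers by more than 0.209 m/s (e = 0.10), 0.105 m/s (e = 0.20) or 0.070 m/s (e = 0.30).
- With g = 0, any shortfall reverses the sign.
- An example of erasure: m = 0.40, g = 0.0418, e = 0.20, v = 0.30. Walkers only: (0.5 × 0.4418 + 0.2 × 0.30) / 0.7 − 0.40 = +0.001. All randomised: 0.5 × 0.0418 + 0.2 × 0.30 = +0.081.

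**4. Recorded speeds only: power.** With the article's effect and SD, 50% walkers leaves about 11.5 per arm and power 0.48 (t). With 70% walkers it is 16.1 per arm and power 0.63.

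**5. Non-walkers scored 0: SD and power.** Assumptions: 50% walk, with mean m and within-walker SD 0.05. Overall SD = √[0.5 × (0.05² + m²) − (0.5 × m)²].

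- m = 0.10: √0.00375 = 0.061; power at 23 per arm 0.62 (t); 34 per arm for power 0.8 (normal formula).
- m = 0.40: √0.04125 = 0.203; power 0.10; 371 per arm.

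These figures keep an all-patient difference of 0.0418 m/s. If that gain occurred only in the 50% who walk, the all-patient difference would be 0.5 × 0.0418 = 0.0209 m/s, and power lower still.

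**6. Choice of test with zeros.** In the scenario of step 2, a rank test rejected in 8 to 11% of simulated trials and the t-test in about 6%. The rank test is somewhat better, but neither is well powered at 23 per arm.

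**The case against.** A reader might infer that the plan drops non-walkers and will therefore bias the result. The documents do not support that. Outcome and Analyses mention no walkers-only set and no complete-case rule. The speed is to be assessed at baseline in patients with WISCI 5 or below, and the sample size counts subjects rather than walkers. Both hint that everyone may be scored, though neither proves it. If non-walkers score 0 or take the lowest rank, selection and reversal do not arise.

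Nor is the plan committed to a t-test, since Analyses also allows the non-parametric counterpart depending on the variable. A reader might also take the Abstract to mean that most patients will have no speed at the end of training. It speaks of walking unsupported, which is not the same as being unable to cover 10 m with an aid. Training mostly ends around or after the three-month mark, and speed is measured again at six months. The share without a speed is therefore unknown. WISCI, which is closer to the stated hypothesis, is already collected.

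All of this stands and limits the claim. It could also be said that a scoring rule is a detail for the full protocol. That answers less, because the article itself fixes the variable, the eligible range and a sample size that fits neither reading once an appreciable share cannot walk 10 m.

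**Conclusion.** The concern holds in a conditional form. The article fixes a primary variable that has no stated value for part of its own eligible population, and sizes the trial as if every patient had one.

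- If recorded speeds alone are compared, a real benefit can be erased or reversed (0.400 v 0.314 m/s among walkers, against 0.20 v 0.22 m/s over all randomised). Reversal is possible, not inevitable; it depends on how many extra patients walk and how slowly.
- If non-walkers are scored 0, the SD rises from 0.05 to about 0.06 to 0.20 m/s and power at 23 per group falls from 0.8 to about 0.62 to 0.10.

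The walking shares, the walkers' speeds and the within-walker SDs other than 0.05 are assumptions. The 50% share echoes the article's figure for ASIA B, which is not a figure for this sample at the end of training. The absence of a rule in the article is certain; the size of its effect is illustrative.

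**What to change.** 1. In Outcome, state that all randomised patients are analysed and that anyone unable to complete the ten-metre test with their permitted aid is given 0 m/s, the lowest rank.
2. In Analyses, name the rank-based option already allowed there as the primary test for walking speed. Adjustment for ASIA grade is optional.
3. Report by arm the proportion able to walk 10 m and the WISCI distribution. Do not present speed among walkers as a between-arm effect.
4. In Subjects, restate the SD and power for this outcome, with the assumed proportion of walkers given openly.

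Cost: items 1 to 3 change wording only and use data already collected. The headline result becomes a rank measure, with the mean difference in m/s as a supporting estimate. Item 4 has a real price. The stated power becomes less favourable, and the sponsor must either accept that at 23 per group or recruit more patients.

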### Analyses

All analyses will be performed in the leading center by the PI. He receives the data in form of an electronically completed case record form after completion of the training. For the analyses, the data will then be incorporated into the statistical software (PASW statistics 17.0, IBM-SPSS Inc. Chicago/IL).

In order to describe the characteristics of the sample, descriptive statistics will be applied. For the analysis of training induced differences between intervention and control group, T-Test for independent groups or the non-parametric correspondent depending on the outcome variable will be applied. In addition, multilevel models will be used to evaluate potential confounding factors (e.g. center effects, age differences, neurological level of lesion or ASIA) as required.
